### Data management

#### Source data

Source documents are original documents, data, and records from which participants’ study data are obtained. These include, but are not limited to, hospital records (from which medical history and previous and concurrent medication may be summarized into the CRF), digital or printed laboratory and pharmacy records, MRI data files and digital or printed output from monitoring devices. CRF entries are considered source data if the CRF is the site of the original recording (that is, no other written or electronic records of the data exist). In this study, the CRF is used as the source document for some clinical data points. Whenever possible, clinical laboratory data (hematology/biochemistry, etc.) are downloaded directly from the analyzers into the study database.

All documents are stored safely in secure, confidential locations. In order to maintain patient confidentiality, only the signed informed consent form, the patient master log, and the trial drug documents are labeled with the patient’s name or identifying information. All other study documents are identified by the subject number and initials only. Data recorded on paper are entered on site into the database in accordance with standard operating procedures and monitored for accuracy.

Where possible, patients admitted to the HDU/PICU who might potentially be eligible for the study are monitored on systems with the facility for subsequent automatic download of hemodynamic parameters. If the patient does enter the trial and gives appropriate consent, then these data for up to 2 h prior to enrollment are downloaded together with the information for the 72 h after enrollment.

#### Quality control and quality assurance procedures

The study will be conducted in accordance with the current approved protocol, Viet Nam Guidelines for Good Clinical Practice, and study standard operating procedures. The OUCRU Clinical Trials Unit will be engaged in assuring good governance, regulatory compliance, and QA/QC of study execution. Any changes to study documents will be approved by the responsible ethics committee as required and communicated to all study staff by the Principal Investigator before implementation.

#### Trial monitoring

The trial is being monitored according to procedures defined by the OUCRU Research Governance Team to ensure that the rights and safety of patients are protected, and that data are generated, documented, and reported in compliance with the protocol, standard operating procedures, and the appropriate regulatory requirements. Periodic onsite monitoring will take place to verify source documents for study data quality and regulatory compliance according to a risk-based monitoring plan.

#### Data sharing

The final data set will be anonymized and made available through governed sharing mechanisms to external investigators for use in secondary analyses.

### Statistical considerations

#### Sample size

During 2011, approximately one-third of patients with Grade 3 HFMD managed at HTD (48/140, 34 %) and CH1 (48/148, 32 %) required milrinone for ANS dysregulation with hypertension, and in 9/48 (19 %) of the HTD cases and 10/48 (21 %) of the CH1 cases, milrinone, when used alone, failed to control the hypertension (personal communication, [name] [name]). Following introduction of new Vietnamese MoH management guidelines to commence intra-arterial BP monitoring early (at the first sign of autonomic disturbance), among 16 children managed in this way at HTD over a 2-month period, 12/16 patients developed Stage 1 hypertension, and seven of these 12 cases developed Stage 2 hypertension and were treated with milrinone. Based on this observation (that is, that 7/12 children with Stage 1 hypertension progressed), for the sample size calculation for this study, we estimated a progression rate of 50 % in the control arm.

With respect to the hypothesized treatment effect, little direct information exists for the actual scenario we plan to investigate, that is, the influence of MgSO_4_ commenced at Stage 1 hypertension on subsequent control of SBP and progression to severe disease. In the case series described earlier, when MgSO_4_ was added to the treatment regimen of patients with poorly controlled hypertension, despite high-dose milrinone, in all cases, the SBP reduced within 30 to 60 min and thereafter remained stable on a continuous MgSO_4_ infusion. In the tetanus study mentioned above (in which the study drug was given to patients with severe tetanus requiring a tracheostomy), the requirement for additional therapy to treat ANS dysfunction was reduced from 14/97 (14 %) in the placebo group to 3/97 (3 %) in the MgSO_4_ group, although the need for assisted ventilation was similar in the two groups. Thus, indirect evidence suggests that the effect size of the proposed intervention may be large; we therefore estimate that use of MgSO_4_ could reduce the risk of progression by > 50 %.

Based on 1:1 randomization, an anticipated relative reduction in the risk of progression of 50 % (from 50 % in the control arm to 25 % in MgSO_4_ recipients), 90 % power, and a two-sided 5 % significance level, 85 patients per treatment group are required. To allow for some violations of our assumptions and losses to follow-up, we plan to recruit 190 patients (95 patients per treatment arm) into the study.

#### Statistical analysis

All planned statistical analyses will be pre-defined in a detailed statistical analysis plan, which will be finalized prior to unblinding the trial. The primary analysis population will include all randomized patients who commenced the loading dose infusion of the study drug, and analysis will be according to the randomized treatment arm (intention-to-treat). A per protocol analysis will also be performed, including all subjects who complete the full treatment schedule for 72 h or if death or one of the pre-specified criteria for stopping the study drug occurs within 72 h. An additional analysis will also be performed in the subgroup of patients with confirmed EV71 infection. The primary endpoint of disease progression will be compared between the two treatment arms based on logistic regression with the treatment assignment as the only covariate. As disease progression is evaluated in a short time frame, that is, within 72 h of study drug initiation, we expect to lose only a minimal number of patients to follow-up before that time point and will analyze these patients according to their last recorded disease status. We will also perform regression analysis, including a number of baseline covariates – age, sex, BMI, day of illness at study entry, study site, and baseline severity assessed in terms of an internationally recognized score (PRISM III).

Predefined secondary endpoints and exploratory investigations will be compared between the two treatment arms based on linear regression for continuous endpoints, logistic regression for binary endpoints, and Cox regression for time-to-event endpoints. For laboratory markers, analyses will be adjusted for the pre-dose value of the respective marker. For host genetics analyses in this sample, putative severity alleles will be detected by filtering and comparison with reference data from control groups including the 1000 Genomes Project. For alleles with significant enrichment among severe cases, validation will be attempted using samples from other cohorts with severe HFMD.

The values for CO, SVR, catecholamine, and cytokine measurements will also be correlated with clinical information using descriptive statistical methods. Clinical information including temperature, skin perfusion, capillary refill time, respiratory rate, and urine output will be summarized for defined time intervals (6 hourly), and relations will be assessed with the cardiovascular and biochemical markers measured during the same time interval.

All AEs and SAEs will be recorded in the patient CRF, and reported to the relevant authorities as indicated previously. In addition, for analysis of safety endpoints, the intensity of clinical and laboratory AEs are graded on a five-point scale adapted from the NIH guidelines (CTCAE version 4.03) [29] to ensure that the cutoffs used are appropriate to the age of the population being studied (Additional file 1: Appendix 10).

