All patients aged 6 months to 15 years admitted to the PICU at HTD or the HDU on the Infectious Diseases Ward at CH1 in Ho Chi Minh City with clinically suspected HFMD (Additional file 1: Appendix 1) are considered for eligibility for this trial. Patients are eligible for enrollment if a) the arterial blood pressure (BP), measured via an indwelling catheter, exceeds the internationally recognized definition for Stage 1 hypertension in children (Additional file 1: Appendix 3) [27]; b) they exhibit at least one other criterion for ANS dysregulation (Additional file 1: Appendix 4), such as tachypnea for age, irregular or labored breathing but with oxygen saturation above 92 % in air and a normal arterial blood gas, resting heart rate sustained above 150 beats/minute, mottled skin, profuse sweating, refractory fever, or hyperglycemia; and c) no contraindications to study inclusion are present, including a past history of hypertension, chronic renal, cardiac or pulmonary disease, or any neurological disorder; features indicating a current hypertensive emergency (see below); treatment with milrinone or any other inotropic agent has already commenced; respiratory distress is present with oxygen saturation below 92 % in air or an arterial pCO_2_ over 45 mmHg; atrioventricular block or any arrhythmia (other than sinus tachycardia) is present on an ECG rhythm strip, or the QT interval is prolonged; or reduced urine output or increased creatinine levels indicate renal compromise. If the patient fulfils these criteria and a parent or guardian gives written informed consent (see “Ethical Considerations” section), then the child is enrolled in the study.

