### Criteria for the addition of milrinone

Milrinone will be commenced in any of the following circumstances to ensure compliance with the Vietnamese MoH guidelines for management of HFMD:Hypertensive emergency, which includes a severe symptomatic elevation in BP (>30 % compared to baseline BP) WITH evidence of acute target organ damage, for example, brain (seizures or increased intracranial pressure), kidneys (renal insufficiency), eyes (papilledema, retinal hemorrhages, or exudates), or heart (heart failure).For children aged 1 year and older:SBP increases to ≥ 99th percentile plus between 5 and 15 mmHg consistently for 30 min.SBP increases to ≥ 99th percentile plus 15 mmHg consistently for 15 minSBP increases to ≥ 40 mmHg over baseline for 15 min and this value is lower than either of the first two cut-offs. The baseline SBP is defined as the lowest value measured at any time after admission to hospital before enrollment in the study.For children aged 6 months to 1 year:SBP increases to ≥ 110 mmHg up to 120 mmHg consistently for 30 min.SBP increases to ≥ 120 mmHg consistently for 15 min.

Occasionally, the clinical status of a patient may indicate that milrinone is not the best inotrope to use. In these cases, the treating physician will make management decisions appropriate to the situation. Similarly, if the patient’s clinical status remains unstable after starting milrinone, additional measures, including ventilation and/or hemofiltration, will be considered in accordance with Vietnamese MoH guidelines for management of HFMD (Additional file 1: Appendix 2). If the BP remains high (SBP > 99th percentile plus > 15 mmHg) despite maximal doses of milrinone and study drug infusion, then additional antihypertensive agents may be added, such as nicardipine, captopril, etc. depending on the clinical scenario.

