#### Randomization and blinding

Randomization follows a 1:1 ratio, stratified according to the hospital where recruitment takes place. A randomization list using block randomization with blocks of variable size has been prepared by the Clinical Trial Pharmacist using a computer program and is maintained confidentially from all study staff and treating doctors, including those assessing all trial outcomes. A chronological log of all enrolled patients is maintained by the Pharmacist and the next available sequential study code is assigned to each patient as they enroll. The assigned number corresponds to a coded, sealed, package containing 50 ampoules of 15 % MgSO_4_ or visually matched placebo.

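### The primary logistic model omits the stratifying hospital and entry systolic pressure: the test is valid, but adjusting would be cheap and modestly more efficient

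*Protocol article*

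**What the plan says.** Randomization and blinding: "Randomization follows a 1:1 ratio, stratified according to the hospital where recruitment takes place".

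Statistical analysis: the primary endpoint is compared by "logistic regression with the treatment assignment as the only covariate". A further regression is planned with "age, sex, BMI, day of illness at study entry, study site, and baseline severity assessed in terms of an internationally recognized score" (PRISM III). Hospital is therefore adjusted for, but only there. SBP at entry is in neither model. The same section does adjust laboratory markers for their pre-dose value.

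SBP at entry is known. Under the eligibility criteria the arterial pressure, "measured via an indwelling catheter, exceeds the internationally recognized definition for Stage 1 hypertension in children", decides entry. The Source data section adds that, where the monitoring system allows it, "these data for up to 2 h prior to enrollment are downloaded".

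SBP also drives the outcome. The composite includes the blood-pressure criteria for adding milrinone, which are mostly SBP thresholds. The Criteria for the addition of milrinone section uses the term baseline for a different quantity: "The baseline SBP is defined as the lowest value measured at any time after admission to hospital before enrollment in the study".

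**The concern.** When randomisation is stratified by a factor, the usual practice is to carry that factor into the primary model. If the factor predicts outcome, an analysis that ignores it has a standard error slightly too large for the design.

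Entry SBP matters more. One component of the composite is, in the main, SBP reaching a threshold, so a child who starts close to it is more likely to have an event. The protocol enrols mostly Stage 1 children but also allows a few at Stage 2, which it describes as roughly the level at which milrinone is indicated. Distance from that level at the start of infusion should therefore be prognostic. Leaving it out gives up some power and leaves any chance imbalance between arms uncorrected. What is at stake is the efficiency of the primary test, which matters most if the true effect is smaller than planned. The Discussion concedes that the assumed effect is large and that reliable baseline outcome data are lacking.

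**Working it through.** **1. The plan's own sample size.** Inputs (Sample size section): 50% v 25%, two-sided 5%, 90% power.
- Mean proportion 0.375, so √(2 × 0.375 × 0.625) = 0.6847; √(0.25 + 0.1875) = 0.6614.
- n = (1.960 × 0.6847 + 1.2816 × 0.6614)² / 0.25² = 76.7, that is 77 per arm.
- With continuity correction: (76.7/4) × [1 + √(1 + 4/(76.7 × 0.25))]² = 84.5, that is 85 per arm, as stated.
- 85/0.90 = 94.4, that is 95 per arm (190 in total).

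**2. Power of the unadjusted test at 95 per arm.** Φ[(√95 × 0.25 − 1.960 × 0.6847)/0.6614] = Φ(1.655) = 95.1%. The 90% target is met without covariates.

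**3. Events available.** 95 × 0.50 + 95 × 0.25 = 47.5 + 23.75 = about 71, ample for two more terms.

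**4. Hospital.** Milrinone need in 2011 was 48/140 (34%) and 48/148 (32%). Odds ratio = (48/92)/(48/100) = 1.09.

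**5. Simulated power, 95 per arm.** Two-sided Wald tests from logistic models, with marginal risks held at the stated values. Assumptions: two hospitals of equal size, blocks of four within hospital, and a standardised entry SBP with the odds ratio per SD shown. 4,000 trials per row for 50% v 25% (hospital odds ratio 1.1) and 3,000 for 50% v 33% (1.09).

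| Truth | SBP odds ratio per SD (assumed) | Treatment only | + hospital | + SBP | + both |
|---|---|---|---|---|---|
| 50% v 25% | 1.0 | 94.7% | 94.8% | 94.8% | 94.7% |
| 50% v 25% | 1.5 | 94.9% | 95.0% | 95.3% | 95.4% |
| 50% v 25% | 2.0 | 95.0% | 95.1% | 96.4% | 96.4% |
| 50% v 25% | 3.0 | 95.1% | 95.2% | 97.9% | 97.9% |
| 50% v 33% | 1.5 | 63.8% | 63.8% | 65.8% | 65.9% |
| 50% v 33% | 2.0 | 63.5% | 63.7% | 68.7% | 68.9% |
| 50% v 33% | 3.0 | 64.2% | 64.5% | 72.6% | 72.8% |

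Hospital adds about 0.1 point at the planned effect. At an assumed hospital odds ratio of 2 it adds about 0.2 to 0.4 point, or 1.5 points at 50% v 33%. The Monte Carlo standard error of a single power figure is √(0.95 × 0.05/4000) = 0.3 point in the upper rows and √(0.64 × 0.36/3000) = 0.9 point in the lower. The models in a row were fitted to the same simulated trials.

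**6. Stage at entry as the covariate, 95 per arm.** Assumed event rates are 92% v 80% in Stage 2 and 50% v 25% in Stage 1; 6,000 trials per row.

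| Stage 2 share (assumed) | Overall event rates | Unadjusted | Adjusted for stage |
|---|---|---|---|
| 5% | 52% v 28% | 93.5% | 94.7% |
| 10% | 54% v 31% | 90.8% | 93.2% |
| 20% | 58% v 36% | 87.7% | 92.7% |

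Overall rates are weighted means, for example 0.1 × 92 + 0.9 × 50 = 54.2%. A second run of 3,000 trials gave 91% v 94% at a 10% share.

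**7. Type I error.** With both arms at 50%, rejection was 4.7% to 5.4% in all four models of step 5.

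**8. Chance imbalance.** The difference between arms in mean standardised SBP has SD √(2/95) = 0.145, so a 95% range of about ±0.28 SD. At an assumed odds ratio of 2 per SD, 0.28 × ln 2 = 0.19 on the log-odds scale, against a planned effect of ln 3 = 1.10. That is roughly a sixth of the effect, and adjustment would remove it.

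**The case against.** The strongest reply is that nothing here is wrong. The sample size was computed for an unadjusted two-proportion comparison, and the analysis matches it. The test holds its level, the 90% target is met, and an adjusted regression including study site is already planned. The unadjusted model also gives a marginal odds ratio directly, while an adjusted logistic model gives a conditional one. All of that stands and sets the weight of the point.

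It can also be said that covariate detail belongs to the statistical analysis plan, which is not shown. That has some force for the additional covariate list. It has less for the primary model, which the article states outright.

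A third reply is that the covariate is not ready-made. From age 1 year there are several SBP criteria with different durations, one of them relative to the lowest pre-enrolment value; infants have fixed bands; and the monitor download is conditional. This also stands, but it asks only for one simple definition, since an arterial reading is needed for eligibility.

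A reader might infer three stronger things. First, that ignoring the stratification makes the primary test invalid: the simulated type I error does not bear that out, and with 34% v 32% the effect on the standard error is negligible. Second, that 5 or more points of power are being lost: at the planned 50% v 25%, even an SBP odds ratio of 3 per SD gives about 3, and the stage scenario reaches 5 only at a 20% Stage 2 share, whereas the protocol expects few such children. Third, that adjustment is entirely free: the change in the odds ratio's meaning is a small but real cost.

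**Conclusion.** The point holds as an efficiency and chance-imbalance improvement, not as an error. The primary model omits the stratification factor, and entry SBP is missing from both the primary model and the additional covariate list.

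Hospital contributes almost no power on the protocol's own figures; the reason to include it is consistency with the stratified design. The gain from entry SBP is about 0 to 3 points at 50% v 25%, about 1 to 3 points if 5% to 10% of children enter at Stage 2, and about 2 to 8 points if the true effect is 50% v 33%. The direction follows from how the endpoint is built. The size rests on assumed odds ratios per SD (1.0 to 3), or on assumed Stage 2 event rates and shares, none of which the documents supply.

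**What to change.** Before unblinding, specify the primary model as treatment + hospital + SBP at infusion start.

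- Define SBP at infusion start in one simple way, for example the last arterial reading before the loading dose, expressed as mmHg above the child's 99th percentile, or as Stage 1 or 2. State how the definition applies to infants. Do not use the milrinone section's baseline value, which is the lowest pre-enrolment reading.
- Report the standardised risk difference and risk ratio alongside the conditional odds ratio.
- Keep the treatment-only model as a supportive analysis.
- Add entry SBP to the covariates of the additional regression.

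The cost is wording in the statistical analysis plan and the work of defining the covariate in advance. No new measurement is needed, because arterial pressure is already taken for eligibility. The downside is that the odds ratio becomes conditional, which the standardised measures address.

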### Study endpoints

*The primary endpoint* is a composite endpoint indicating disease progression within 72 h. It is defined as the occurrence of any of the following within 72 h of commencing the study drug infusion:Specific BP criteria necessitating the addition of milrinone as detailed in the section “Criteria for the addition of milrinone” below.Need for mechanical ventilation.Development of shock.Death.

*Secondary endpoints* comprise these parameters singly, plus a number of other clinical endpoints including the following: a requirement for other inotropic agents (for example, dobutamine), duration of hospitalization, presence of neurological sequelae at discharge in survivors, and neurodevelopmental status assessed 6 months after discharge.

*Safety endpoints* include the number of adverse events (AEs) and severe adverse events (SAEs) that occur in the two treatment arms.

*Exploratory endpoints* will be assessed, including serial measurements of cardiac output (CO) and systemic vascular resistance (SVR), catecholamine levels, and cytokine levels. We will assess the impact of MgSO_4_ on these parameters, provided the data collected appear reliable and consistent within individual participants.

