#### Withdrawal of participants from the study

Dedicated study staff members are employed to support parents/guardians to meet study visits and ensure that all trial outcome data are collected. Parents/guardians of the study participants may voluntarily withdraw from the study for any reason. If this occurs, the child will be managed in accordance with standard clinical care guidelines. With the agreement of the parent/guardian, a clinical assessment will be performed and recorded at the time of withdrawal, and the reason for withdrawal will also be recorded in the CRF.

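### Children lost before 72 h with no recorded event are counted as observed non-events in the primary analysis; the effect is small unless loss is about 5% or more and unequal, or the result is borderline

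*Protocol article*

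**What the plan says.** All statements are in the protocol article.

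- **Study endpoints.** The primary endpoint is a composite of milrinone blood-pressure criteria, mechanical ventilation, shock or death: "It is defined as the occurrence of any of the following within 72 h of commencing the study drug infusion".
- **Statistical analysis, population.** "The primary analysis population will include all randomized patients who commenced the loading dose infusion of the study drug", analysed by randomized arm. A child who starts the infusion and is then lost stays in the denominator.
- **Statistical analysis, model.** The arms are compared "based on logistic regression with the treatment assignment as the only covariate". This model has no censoring.
- **Statistical analysis, early loss.** Because the window is short, "we expect to lose only a minimal number of patients to follow-up before that time point". For those who are lost, the investigators "will analyze these patients according to their last recorded disease status".
- **Withdrawal of participants from the study.** Parents or guardians "may voluntarily withdraw from the study for any reason". A clinical assessment is made at that time if they agree, and the child then receives standard care.
- **Clinical assessments and follow-up.** Participants stay in the study to 6 months unless the parent or guardian withdraws them.
- **Sample size.** The planned risks are 50% and 25%, which need 85 per arm. "To allow for some violations of our assumptions and losses to follow-up, we plan to recruit 190 patients", that is, 95 per arm.

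**The concern.** The last-status rule is a single imputation. A child taken out of the study at 12 h with no component recorded has a last status of not progressed. The model then treats that child as if all 72 h had been observed without an event. The protocol expects half of the control children to progress, so for an individual child this is the most optimistic value available, and it enters as if it were known.

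Withdrawal may follow worsening that has not yet met a component, so it need not be independent of outcome or equal between arms. If loss is unequal, the arm that loses more children appears to do better. The primary comparison is at stake, and so is the reading of a result close to P = 0.05.

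**Working it through.** **The plan's own figure.** Inputs from Sample size: risks 0.50 and 0.25, two-sided 5%, 90% power, 1:1.

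- Pooled formula: n = [1.96·√(2·0.375·0.625) + 1.2816·√(0.25 + 0.1875)]² / 0.25² = 76.7.
- With continuity correction: (76.7/4)·[1 + √(1 + 4/(76.7·0.25))]² = 84.5, so 85 per arm. This reproduces the protocol.
- Allowance: 1 − 85/95 = 10.5%.

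The protocol gives no early-loss rate. Every loss rate L below is an assumption, with 95 per arm throughout. Ordinary risk means that lost children carry their arm's full 72-h risk, as if all left at the start. Children who stay event-free for some hours first have less risk left, so under uninformative loss this overstates the distortion.

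**1. Equal loss in both arms, ordinary risk.** The rule turns 0.50 and 0.25 into 0.50(1 − L) and 0.25(1 − L). The ratio stays 0.50.

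| L | Control | MgSO4 | Difference (points) | Power |
|---|---|---|---|---|
| 0% | 50.0% | 25.0% | 25.0 | 95.1% |
| 2% | 49.0% | 24.5% | 24.5 | 94.5% |
| 5% | 47.5% | 23.75% | 23.8 | 93.4% |

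**2. Equal loss, all lost children would have progressed.** The rates become 0.50 − L and 0.25 − L. The difference stays at 25 points. The relative risk moves to 0.23/0.48 = 0.48 at 2% and 0.20/0.45 = 0.44 at 5%, which exaggerates the benefit on the ratio scale.

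**3. No true effect (50% in both arms), loss in one arm only.** With d the spurious difference, SE₀ the pooled and SE₁ the unpooled standard error, the rejection probability is Φ[(d − 1.96·SE₀)/SE₁] + Φ[(−d − 1.96·SE₀)/SE₁]. Both standard errors are about 0.0725.

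| L | Lost children | Rate in that arm | d | Two-sided type I error |
|---|---|---|---|---|
| 2% | ordinary risk | 49.0% | 0.010 | 0.034 + 0.018 = 5.2% |
| 2% | all would progress | 48.0% | 0.020 | 0.046 + 0.013 = 5.9% |
| 5% | ordinary risk | 47.5% | 0.025 | 0.053 + 0.011 = 6.4% |
| 5% | all would progress | 45.0% | 0.050 | 0.102 + 0.004 = 10.6% |

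**4. Recoding lost MgSO4 children as events** (chi-square without continuity correction).

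- Borderline result, 48/95 v 34/95: z = 0.1474/0.0719 = 2.05, P = 0.040. One recoded child gives 48 v 35: z = 0.1368/0.0720 = 1.90, P = 0.057.
- Planned effect, 48/95 v 24/95: z = 0.2526/0.0704 = 3.59, P = 0.0003. Ten recoded children give 48 v 34, P = 0.040. The eleventh takes P above 0.05.

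**The case against.** The strongest defence is that the rule will rarely operate. These are PICU or HDU inpatients with arterial monitoring during a 72-h infusion, the protocol expects minimal loss, and it states its rule and reason openly. A child who meets a component before leaving is still a failure. Side effects that stop the drug do not end follow-up. The per-protocol analysis would leave out a child withdrawn early without a stopping criterion, which gives a rough check, although it drops such children rather than counting them as progressed. All of this stands and limits the size of the point. It does not make the rule a good one, because its error grows when loss is unequal or related to outcome.

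Four stronger readings are tempting, and the document does not support them.

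- **The rule favours MgSO4.** It applies to both arms. Equal uninformative loss narrows the risk difference, and greater loss among controls would work against MgSO4.
- **The 20-child margin (190 − 170) reveals 10 early losses per arm.** That margin also covers violated assumptions, and follow-up runs to 6 months, so it neither predicts 10% loss before 72 h nor contradicts the expectation of minimal loss. Scenarios built on it are assumed extremes. One example is 42/95 v 31/95 (relative risk 0.74, P = 0.10), where all ten lost MgSO4 children progress and no lost control does.
- **No sensitivity analysis is planned.** The article defers the detailed analyses to a statistical analysis plan that is not shown, so their absence here is not a finding.
- **The confidence interval is materially too narrow.** Treating imputed values as observed does understate uncertainty in principle, but at minimal loss the amount is negligible.

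**Conclusion.** The point holds and is minor. The protocol fixes a primary-analysis rule under which a child lost before 72 h without a recorded component becomes an observed non-event. At 2% loss confined to one arm, type I error is at most about 5.9%, even if every lost child would have progressed. The rule becomes a practical concern if early loss reaches about 5% or more and differs between arms (6.4% to 10.6%), or if the result is close enough to P = 0.05 for one child to decide it. A result at the planned effect would survive the recoding of ten MgSO4 children.

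These sizes rest on assumed loss rates, 50% true risk in both arms for the type I error figures, 95 per arm and a normal approximation. They show how the rule behaves and do not forecast bias in this trial.

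**What to change.** Make the change in the statistical analysis plan, which the protocol says will be finalized before unblinding.

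1. Where the family agrees, record the four components up to 72 h from hospital records after a child is withdrawn from the study. Hospital records are already listed as source documents.
2. For children still missing, replace the last-status rule with a 72-h risk that censors at the last observation (Kaplan-Meier or Cox), or with multiple imputation using baseline data and the SBP course. Censoring assumes that loss is uninformative given what is modelled, so it needs step 3 beside it.
3. Report a sensitivity analysis that counts lost children as progressed, and give the number and timing of early losses by arm.

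The cost is some plan wording, a little chart review and a little analysis work. The sample size does not change.
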